Number of physiotherapy consultations for GP referrals, ‘true self-referral’ and ‘recommended self-referral’ patients in the intervention practices
Number of self-referring patients deemed unsuitable at each stage in the direct access pathway
Onward referral rate from physiotherapy (to GP, other services) for GP referrals, ‘true self-referral’ and ‘recommended self-referral’
Physiotherapy waiting time (month-by-month) from 12 months prior to introduction of direct access to end of study
Number of patient complaints about direct access at physiotherapy site
Monitoring of safety
Number of cases of missed serious pathology in patients directly accessing physiotherapy
Number of adverse events in GP-referred, ‘true self-referral’ ‘recommended self-referral’

^a^Those who are prompted by their GP or practice nurse to access physiotherapy care

^b^Those who directly access physiotherapy care without prompting by their GP or practice nurse

Clinical outcomes: Data collection will include the collection of clinical and cost data through patient self-report questionnaires at baseline and 2, 6 and 12 months follow-up. The primary clinical outcome is physical health measured using the SF36v2 Physical Component Summary. A summary of the clinical outcomes and other measures included in each questionnaire is shown in Table 2.

**Table 2 Tab2:** STEMS pilot trial questionnaire measures

Domains	Description				
		Baseline	2 months	6 months	12 months
Primary outcome measure					
Physical function	SF36v2 physical component summary http://www.sf-36.org/	✓	✓	✓	✓
Secondary outcome measures					
Overall change in condition	Global assessment of change since baseline—single question	✘	✓	✓	✓
Mental health	SF36v2 mental component summary http://www.sf-36.org/	✓	✓	✓	✓
Quality of life	EuroQol EQ-5D-5 L www.euroqol.org	✓	✓	✓	✓
Self-efficacy	Pain self-efficacy questionnaire (PSEQ) [31]	✓	✓	✓	✓
Understanding of condition	General practice assessment questionnaire enablement subscale [32]	✓	✓	✓	✘
Experience of consultations	General practice assessment questionnaire communication [32]	✓	✓	✓	✘
Accessibility of services	Single question	✘	✓	✓	✘
Satisfaction with services	Single question	✘	✓	✓	✘
Baseline measures					
Demographics	Gender, date of birth, ethnicity, education, health literacy, employment status, socio-economic status (recent paid job title, housing)	✓	✘	✘	✘

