Baseline risk of persistent problems	STarT Musc tool (draft tool developed at Keele University to identify patients’ risk of persistent pain and disability)	✓	✘	✘	✘
Pain location	Body manikin	✓	✘	✘	✘
Pain duration	Single question about duration of pain	✓	✘	✘	✘
Comorbidities	Single question	✓	✘	✘	✘
Economic outcomes					
Further health care utilisation	Consultations, investigations, procedures, admissions, over-the-counter medications	✘	✘	✓	✓
Work absence	Single question	✓	✓	✓	✓
Presenteeism	Single work performance question	✓	✓	✓	✓
Willingness to pay	Three willingness to pay questions	✘	✘	✘	✓

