All patients will be asked to complete the 5-level version of the EuroQoL-5D (EQ-5D) questionnaire at baseline, 6 months and 12 months in order for the quality-adjusted life years (QALYs) over the 12-month time period to be calculated for each participant. The QALYs combine information on health-related quality of life and survival.

Resource use will be multiplied by unit costs obtained from standard sources (NHS Reference Costs, British National Formulary, Unit Costs of Health and Social Care) and healthcare providers. Due to the lack of nationally representative unit cost estimates for private healthcare, this care will be costed as the NHS equivalent in the base case. Patient reported costs for over-the-counter treatments will be used. Productivity costs will be calculated using data collected on employment status at every time-point and days off work due to their musculoskeletal problem. For those in paid employment, information on occupation and the nature of their employment (full time or part time) will be requested. The average wage for each respondent will be identified using UK Standard Occupational Classification coding and annual earnings data for each job type. The analysis will use the human capital approach, and the self-reported days of absence will be multiplied by the respondent-specific wage rate. The human capital approach assumes that the value of lost work is equal to the amount of resources an individual would have been paid to do that work and values productivity losses as a result of morbidity (or mortality) by measuring time lost from work and multiplying this with the gross wage of the person. Responses to the EQ-5D questionnaire at baseline and 6 and 12 months will be used to calculate QALYs for each participant using the area under the curve method.

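### The QALY rule uses EQ-5D at baseline, 6 and 12 months, although Table 2 also schedules it at 2 months; employment status for productivity costs shows a similar but smaller mismatch

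*Protocol article*

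**What the plan says.** **QALYs.** The Health economic analysis section of the protocol article gives the EQ-5D timing twice. On collection, patients complete the "questionnaire at baseline, 6 months and 12 months in order for the quality-adjusted life years (QALYs) over the 12-month time period to be calculated". On analysis, where the stated method is area under the curve: "Responses to the EQ-5D questionnaire at baseline and 6 and 12 months will be used to calculate QALYs for each participant". Neither sentence mentions 2 months.

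Table 2, under Outcome measures, has the row "EuroQol EQ-5D-5 L www.euroqol.org" among the secondary outcomes, with ticks at baseline, 2, 6 and 12 months.

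**Productivity costs.** The same economic section states: "Productivity costs will be calculated using data collected on employment status at every time-point and days off work due to their musculoskeletal problem". In Table 2, employment status appears only in the demographics row ("Gender, date of birth, ethnicity, education, health literacy, employment status, socio-economic status (recent paid job title, housing"), which is ticked at baseline and crossed at 2, 6 and 12 months. The work-absence and presenteeism questions are ticked at all four time-points.

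**The concern.** The text and the table disagree on when EQ-5D is collected, and the analysis sentence turns the shorter list into a rule. If Table 2 is right, a scheduled measurement is left out of the QALY without explanation.

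The omitted point matters for this intervention. The Background argues for early physiotherapy and for letting patients choose it when their need is greatest, and the discussion names shorter waiting times as a possible benefit. If the arms differ in quality of life over the first months, the 2-month questionnaire is where that would show. With three points, the first half-year is a straight line from baseline to 6 months.

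The rule also moves weight onto baseline. The Analyses of clinical outcomes section warns that many baseline questionnaires will be completed after the first consultation and so may not be true baselines.

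For productivity costs, the text relies on repeated employment data that the table does not schedule.

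**Working it through.** The documents state no QALY figure, so there is none to reproduce. The check compares the two schedules.

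**Inputs.** Assessment times are 0, 6 and 12 months (Health economic analysis) or 0, 2, 6 and 12 months (Table 2). The horizon is 12 months and the method is area under the curve. Linear interpolation (the trapezoidal rule) is assumed.

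**Weights.** With time in years, an interior point has weight (next time − previous time)/2. An end point has half its adjacent interval.

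| Assessment | Three points | Four points |
|---|---|---|
| Baseline | (6/12)/2 = 0.25 | (2/12)/2 = 0.083 |
| 2 months | 0 | (6/12 − 0)/2 = 0.25 |
| 6 months | (12/12 − 0)/2 = 0.50 | (12/12 − 2/12)/2 = 0.417 |
| 12 months | (6/12)/2 = 0.25 | (6/12)/2 = 0.25 |

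Each column sums to 1.

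**What the difference amounts to.** Subtracting the columns gives four-point minus three-point QALY = 0.25·u2 − 0.167·u0 − 0.083·u6 = 0.25 × [u2 − (2/3·u0 + 1/3·u6)], where u0, u2 and u6 are the utilities at baseline, 2 and 6 months. The bracket is the gap between the 2-month value and the straight line from baseline to 6 months. The three-point rule therefore loses a quarter of that gap, and nothing if the 2-month value lies on the line.

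**Illustrations.** The documents give no utility differences, so these between-arm differences are assumptions. The baseline difference is set to 0.

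| Difference at 2, 6, 12 months | Three points | Four points |
|---|---|---|
| 0.05, 0, 0 | 0 | 0.25 × 0.05 = 0.0125 |
| 0.10, 0, 0 | 0 | 0.25 × 0.10 = 0.025 |
| 0.05, 0.025, 0 | 0.50 × 0.025 = 0.0125 | 0.0125 + 0.417 × 0.025 = 0.0229 |
| 0.05, 0.05, 0 | 0.50 × 0.05 = 0.025 | 0.0125 + 0.417 × 0.05 = 0.0333 |
| 0.05, 0.05, 0.05 | 0.025 + 0.25 × 0.05 = 0.0375 | 0.0333 + 0.0125 = 0.0458 |

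In the last row the three-point rule keeps 0.0375/0.0458, or about 82 %, of the four-point value.

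**Baseline.** An assumed chance baseline difference of 0.03 contributes 0.25 × 0.03 = 0.0075 QALY on three points and 0.083 × 0.03 = 0.0025 on four, if QALYs are not adjusted for baseline utility.

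**Employment.** The stated calculation multiplies self-reported days of absence by a wage derived from occupation. Table 2 supplies absence at all four time-points, and employment status and recent job title at baseline. The only input missing at follow-up is an updated work status and occupation.

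**The case against.** **Is a transient early benefit plausible?** The limitations section does not expect direct access to be superior on clinical outcomes, and waits are to be equal once a referral is logged. Nothing in the article supports a particular utility gain at 2 months. This stands: the sizes above are illustrations, and only the weights are exact.

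**Is an early benefit lost altogether?** A reader might infer this. The documents support it only for a benefit that has gone by 6 months. A benefit still present then is counted, though understated when the 2-month difference lies above the straight line.

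**Is three points a defensible choice?** The times match the two 6-month recall periods for resource use, and a fourth assessment is another that may be missing. The minimum-data questionnaire for non-responders at 6 and 12 months does not include EQ-5D. The choice could be defended, but the article gives no such reason, and its collection sentence still contradicts Table 2. The reminder postcard and repeat pack are the same at 2 months as at the other time-points, so the 2-month value is not obviously harder to obtain.

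**Does the heavier baseline weight bias the result?** Only for unadjusted QALYs. Adjustment for baseline utility largely removes the concern on either schedule, and may be left to an analysis plan that is not shown.

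**Can productivity costs still be produced?** A reader might infer that they cannot. They can: absence recurs at every time-point and occupation is known from baseline. Table 2 is also described as a summary and may not list every item. Full-time or part-time status, which the text says will be requested, is not in it. Employment status could be asked alongside the work items, so this mismatch is less certain than the one for EQ-5D.

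**Conclusion.** The EQ-5D contradiction is real, and following the written rule would leave out a scheduled measurement. Table 2 is the likelier account of collection: the design has four repeated measures, quality of life is a listed secondary outcome, and the secondary outcomes are to be modelled in the same way as the primary, with estimates at 2, 6 and 12 months.

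Under linear interpolation, the 2-month weight is 0 instead of 0.25 and the baseline weight 0.25 instead of 0.083. The effect on the between-arm QALY difference is a quarter of the 2-month departure from the straight line. For the assumed patterns above, this is 0.0083 to 0.025 QALY.

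The employment mismatch is secondary. Its error is confined to participants who change work status, and work-loss costs enter only the broader-perspective sensitivity analysis, since the base case takes an NHS and personal social services perspective.

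The overall impact is modest. The economic analysis is exploratory and mainly descriptive, and neither the recruitment and retention criteria nor the 20 % direct-access target depends on it. It is worth correcting because the pilot is meant to test these methods for the main trial, where the same rule could be repeated.

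**What to change.** **QALYs.** Calculate the area under the curve from all four scheduled EQ-5D assessments, and correct both sentences in the Health economic analysis section to match Table 2. Report the three-point QALY as a sensitivity analysis. This needs no new data if Table 2 is right. The small cost is one more assessment that may be missing, to be handled by imputation; the article already names multiple imputation for its intention-to-treat analysis. If EQ-5D is in fact not asked at 2 months, Table 2 is the place to correct instead.

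**Productivity costs.** Reconcile the text with Table 2. Either schedule employment status at 2, 6 and 12 months, which costs one item per follow-up questionnaire, or state that baseline status and occupation are carried forward and report this as a limitation, which costs one sentence.

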### Setting and clusters

The setting is primary care in England for adults with musculoskeletal problems (GP practices and linked NHS physiotherapy services). GP practices are the unit of randomisation, and thus, patients follow the care pathways to which the practice is randomised. In this pilot, RCT practices will be stratified only on practice size, but in a main trial, practices would also ideally be stratified by index of deprivation. Randomisation of GP practices will be undertaken by an independent statistician. GP practices will be randomised to one of two arms, either to continue with usual GP-led primary care for musculoskeletal patients with the addition of the offer of a self-referral physiotherapy pathway (intervention group) or to continue with usual GP-led primary care alone (usual care control group). Practices will be randomised according to a computer-generated random numbers stratified by the practice size (small or large) in the ratio 1:1. In a main study, we would plan to further stratify by practice setting and area level deprivation (through minimisation) in order to ensure balance in key practice characteristics in each arm of the trial.

GP practices are eligible to take part if they meet the following criteria: they are within the Vale Royal Clinical Commissioning Group area of Cheshire and the Clinical Research Network (CRN); they are a group practice, currently referring musculoskeletal patients to NHS physiotherapy services; they do not currently offer direct access to physiotherapy; and they are willing to test direct access. The balance between scientific considerations and the need for consent is a known issue for cluster trials [27]. Informed consent for practices to participate will be provided by the senior GP partner in each practice acting as ‘guardian’ for patients in their care. Patients will follow the care to which their practice is randomised with identical patient information for both arms providing general information about the study, explaining that their local musculoskeletal services are being evaluated using patient self-reported clinical outcomes and medical record review. Individual patients will therefore be able to opt out of data collection.

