#### Evidence of selection bias

Since this is a pilot trial with only four clusters randomised, it is likely that there will be some imbalance between participants in each of the treatment arms on one or more baseline characteristics. Baseline comparisons will be carried out to detect any substantial differences between participants recruited from the control and intervention arms. This will be done by scrutinising the baseline table for any serious imbalances in observable baseline variables and the trends of the imbalance if any. The recruitment rates will also be estimated and compared between the control and intervention arms. We will examine the size of any imbalances and decide if there is evidence of systematic selection bias in the types of patients being recruited in control versus intervention arms. Any systematic imbalance in the sense that one arm is consistently favoured by the imbalances may not reflect chance alone and may suggest selection bias.

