#### Health economic analysis

The economic analysis will be exploratory, with the aim to inform the design of a full cost-utility analysis alongside a future main trial. A cost-consequence analysis will be reported, describing all the important results relating to costs and consequences for direct access to physiotherapy and usual care arms of the trial. Results will be presented from a health service perspective and a broader societal perspective taking into account patient-incurred costs and productivity losses. An exploratory willingness to pay (WTP) study [37] will also be conducted to assess the use of this methodology to measure broader benefits of direct access.

Data on costs will be sought from all participants and from a broad perspective, taking into account healthcare, patient and societal costs. Healthcare resource used will be collected using self-completed questionnaires at 6 and 12 months, with a recall period of 6 months in each. Questions will ask patients to recall GP consultations, visits to healthcare professionals, outpatient appointments, investigations or treatments and inpatient stays related to the index condition. Participants will be asked to distinguish between NHS and private practice visits. Resource used for the direct access pathway will be directly recorded and costs attached, staff time (taking into account any increased referrals to physiotherapy), materials (posters, flyers, referral forms) and training sessions. GP medical record review of all participants will provide data on relevant prescribed medications for all musculoskeletal problems. In addition, information on costs borne by the patient (e.g. over-the-counter medicines, devices) will be collected via the self-complete questionnaires. Productivity costs will take into account both absenteeism and presenteeism and will utilise self-report data on employment status, occupation and time off work and reduced productivity at work (presenteeism). As this is a pilot trial, the suitability of questions for collecting cost data directly from patients can be assessed, in order to ensure effective resource use and that cost data collection systems are established for a larger trial.

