As this is a pilot trial this will be an exploratory analysis, with the aim to inform the cost data collection and analysis of a future main larger trial. We will test our methods of collecting cost data, from patient questionnaires and medical record reviews and assess the completeness of the data collected. A cost-consequence analysis will be reported, describing all the important results relating to costs and consequences. Analyses will be mainly descriptive, and all costs and outcomes will be summarised using means and 95 % confidence intervals. The data for costs are likely to have a skewed distribution; therefore, the plan is to explore the nature of the distribution of costs. If the data is not normally distributed, a non-parametric comparison of means (e.g. bootstrapping) will be undertaken.

The base case cost analysis will adopt a NHS and personal social services (PSS) perspective. A broader costing perspective will be considered in a sensitivity analysis, taking into account NHS/PSS costs, patients’ personal expenditure and costs associated with work loss. The robustness of the results will be explored using sensitivity analysis and will explore uncertainties in the trial based data and any assumptions made in the base case analysis.

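### The only stated QALY summary is unadjusted arm means, although baseline EQ-5D carries a weight of 0.25 in the QALY and the arms are expected to differ at baseline

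*Protocol article*

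**What the plan says.** The Health economic analysis section builds the QALY first, as an area under the utility curve (the sentence is cut short here): "Responses to the EQ-5D questionnaire at baseline and 6 and 12 months will be used to calculate QALYs for each participant using the area under". It then gives the reporting method: "Analyses will be mainly descriptive, and all costs and outcomes will be summarised using means and 95 % confidence intervals". The one comparison of means that it names comes straight after a remark that costs are likely to be skewed: "If the data is not normally distributed, a non-parametric comparison of means (e.g. bootstrapping) will be undertaken". No covariate appears in this part of the section.

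The purpose is stated as well: "The economic analysis will be exploratory, with the aim to inform the design of a full cost-utility analysis alongside a future main trial". The form of reporting is a cost-consequence description: "A cost-consequence analysis will be reported, describing all the important results relating to costs and consequences".

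On baseline comparability, Evidence of selection bias says, of the two arms: "Since this is a pilot trial with only four clusters randomised, it is likely that there will be some imbalance between participants". Methods for protecting against sources of bias, and Design considerations and limitations, add a structural reason. Control participants come from people consulting their practice. Intervention participants also include people who go directly to physiotherapy, and the article accepts that these may differ in important ways.

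Other analyses do have named covariates. Analyses of clinical outcomes lists age, area deprivation and widespread pain, with a random effect for practice. Nested willingness to pay analysis lists trial arm, age, gender, health status and income.

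**The concern.** A QALY taken as an area from time zero contains the starting utility. If one pair of practices starts higher than the other, its mean QALY is higher even when direct access does nothing. Bootstrapping deals with skewness and leaves such a difference in place. Since the article expects imbalance and collects baseline EQ-5D from every participant, it is odd that the stated summary makes no use of that measurement for QALYs.

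What is at stake is modest: how the QALY rows of the cost-consequence table are read, and the template handed on to the main trial's cost-utility analysis.

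**Working it through.** **Sample size, from the Sample size section.** 100 consulters per month × 0.80 eligible × 0.50 consenting × 4 practices × 6 months = 960, and 960 × 0.80 = 768. Both match the article. The average is 960 / 4 = 240 participants per practice. Allocation is "stratified by the practice size (small or large) in the ratio 1:1", so two practices per arm is assumed, or 480 participants.

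**Weight of baseline utility.** With trapezoids over 0–6 and 6–12 months, in years:

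QALY = 0.5 × (U0 + U6)/2 + 0.5 × (U6 + U12)/2 = 0.25·U0 + 0.50·U6 + 0.25·U12.

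Table 2 also lists EQ-5D at 2 months. If that point were used, the baseline weight would fall to (2/12)/2 = 0.083. The economic section states the three-point version, so 0.25 applies.

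**Carry-through.** Let d be the baseline difference between arms and b the share of it still present at 6 and 12 months. With no true effect, the difference in raw mean QALYs is d × (0.25 + 0.75·b).

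| d | b = 0 | b = 0.5 | b = 1 |
|---|---|---|---|
| 0.02 | 0.005 | 0.0125 | 0.02 |
| 0.03 | 0.0075 | 0.019 | 0.03 |
| 0.05 | 0.0125 | 0.031 | 0.05 |
| 0.10 | 0.025 | 0.0625 | 0.10 |

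**How large d could be by chance.** The article gives no EQ-5D standard deviation (SD) or ICC, so both are assumed here. The standard error of the baseline difference is

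SE = SD × √[(2/480) × (1 + 239 × ICC)].

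- SD 0.25, ICC 0: 0.25 × √0.00417 = 0.016
- SD 0.25, ICC 0.01: 0.25 × √0.01413 = 0.030
- SD 0.25, ICC 0.03: 0.25 × √0.03404 = 0.046

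An imbalance of 0.03 is thus about one standard error under the middle assumption. Over SD 0.20 to 0.30 and ICC 0.01 to 0.05, the 95% range of chance imbalance (1.96 × SE) runs from about ±0.05 to ±0.14. Multiplied by 0.25, that is at least ±0.012 to ±0.034 QALY. With 60% persistence the factor is 0.25 + 0.75 × 0.6 = 0.70, giving about ±0.03 to ±0.10. Any difference due to the recruitment routes would come on top and cannot be sized from the article.

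No adjusted QALY difference can be computed, since the article gives no EQ-5D means, SD, ICC or within-person correlation.

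**The case against.** **The text does not rule out adjustment.** It says that outcomes will be summarised, which is description. Trial organisation and monitoring mentions a statistical analysis plan, not shown here, that could hold a QALY regression. A reader might infer that the investigators have decided against adjustment, or that the bootstrap is their method for comparing QALYs. The article supports neither: it is silent on adjustment, and the bootstrap sentence follows one about costs. What remains is that the article does fix a reporting method for all outcomes and names no covariate in it, while naming covariates for other analyses.

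**Little depends on it.** This stands. The analysis is exploratory, no cost per QALY is planned, and no progression criterion uses a QALY difference.

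**EQ-5D is modelled elsewhere.** It is a secondary outcome in Table 2, and secondary outcomes are to be analysed similarly to the primary mixed model, which uses all four time-points. That covers EQ-5D scores. QALYs are not mentioned there.

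**The interval already carries chance imbalance.** With SD 0.25 and correlation 0.5 between all time-points, the QALY variance is 0.0625 × (0.375 + 0.3125) = 0.043, so its SD is about 0.21. The 95% half-width of the arm difference is then about 1.96 × 0.207 × √(2/480) = 0.026 without clustering, and about 0.048 with ICC 0.01. The 0.019 lies inside both. This is fair for chance imbalance. It does not cover a systematic difference between recruitment routes, and an imbalance that has been measured need not be left in the estimate.

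**Adjustment is not free.** Analyses of clinical outcomes warns that many baseline questionnaires will follow the first consultation and may already reflect outcome. Conditioning on them could remove part of an early effect. This stands, and it is why both estimates are needed.

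**Conclusion.** The point holds as a low-severity improvement. The only summary stated for QALYs is unadjusted arm means with 95% confidence intervals. The QALY includes baseline utility with weight 0.25, and the article expects baseline imbalance.

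At least a quarter of a baseline utility difference would enter an arm-to-arm reading of the means. It would be tempting to say that the whole difference is counted as a gain or loss from direct access. That would need full persistence to 12 months, which nothing in the article establishes. A within-person correlation of 0.5 would not establish it either, because it does not show how far differences between practices persist.

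The weight of 0.25 follows from the article. The 0.03 imbalance, the SD, the ICC and the persistence behind the 0.019 QALY are assumptions. Nothing decided in the pilot depends on the result.

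**What to change.** In the Health economic analysis section, after the sentence on means and confidence intervals, add a statement along these lines:

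> Any between-arm difference in QALYs will also be estimated by regressing QALY on trial arm and baseline EQ-5D, allowing for practice as in the clinical model, and reported with its 95% confidence interval beside the unadjusted arm means. With four practices neither estimate supports firm inference. Because baseline may be completed after the first consultation, adjustment may absorb some early effect.

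The cost is a few lines of text and one regression on data already collected. The small downside is the possible absorption of an early effect, which reporting both estimates lets the reader see.

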## Methods

### Design

The design is a pilot, pragmatic, cluster RCT in general practice and physiotherapy services. The most appropriate trial design is a simple, two-arm parallel, cluster RCT where GP practices are the units of randomisation (the clusters), yet data are collected from individual patients with musculoskeletal problems (the participants). This design overcomes the problem of contamination between arms and the problems associated with individually consenting and randomising patients to a trial testing service-level changes. A main trial would employ a non-inferiority design as it will be essential that the intervention is as least as good as usual GP-led care in terms of patients’ clinical outcomes (physical health measured using the SF36v2 Physical Component Summary).

A repeated measures design will be adopted, whereby participants will complete the questionnaires at baseline, 2, 6 and 12 months. Each participant’s involvement in the trial is for 12 months, during which time they will all have access to usual GP-led primary care. No analysis of clinical outcomes will be undertaken until the 12-month follow-up time-point.

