### Sample size

As this is a pilot trial, a formal sample size calculation has not been carried out. Using Keele’s Consultation in Primary Care Archive (CiPCA) database of GP practices and symptom and diagnostic Read codes, 25 % of the population in an average-sized GP practice (5000 patients) consults at least once per year with a musculoskeletal problem (1250 patients or 100 patients per month). Given the trial exclusions, we anticipate at least 80 % of consulters to be eligible (80 patients per month per practice), 50 % to respond to the invitation to take part in the research evaluation, provide consent and complete a baseline questionnaire (40 patients per month per practice). With four practices recruiting for 6 months in the pilot trial, we estimate 960 participants at baseline and 80 % follow-up (*n* = 768).

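### The cost comparison (means with 95% intervals, bootstrap if skewed) makes no stated allowance for practice clustering, and no simple bootstrap repairs this with two practices per arm

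*Protocol article*

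**What the plan says.** The Design section states that "GP practices are the units of randomisation (the clusters), yet data are collected from individual patients with musculoskeletal problems (the participants"). Setting and clusters has the practices randomised "stratified by the practice size (small or large) in the ratio 1:1", and Evidence of selection bias gives the number: "Since this is a pilot trial with only four clusters randomised". That makes two practices per arm.

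For the economic data, Health economic analysis states that "all costs and outcomes will be summarised using means and 95 % confidence intervals". It expects skewed costs and continues: "If the data is not normally distributed, a non-parametric comparison of means (e.g. bootstrapping) will be undertaken". The shape of the distribution is the only criterion for choosing the method. Neither this section nor the nested willingness-to-pay analysis mentions practice or clustering.

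Analyses of clinical outcomes is different. Its mixed model for the SF-36v2 PCS has a random effect for practice, and secondary outcomes are to be handled in a similar way. Table 2 lists economic outcomes under their own heading, apart from the secondary outcomes, so that extension does not clearly reach costs.

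**The concern.** A bootstrap deals with skewness. It does not in itself deal with the fact that whole practices were allocated. The costs include GP consultations and prescriptions, and in usual care access to NHS physiotherapy runs through GP referral, so practice habits can plausibly shift the mean cost of everyone in a practice. With two practices per arm, such shifts do not average out. An interval that leaves them out of its error can present an ordinary difference between two pairs of practices as a precise effect of direct access on cost.

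An early estimate of costs in each arm is one of the pilot's research objectives, and the economic work is meant to inform the main trial's cost data collection and analysis. The precision attached to the cost difference is therefore one of the things a reader will take from the pilot.

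**Working it through.** **The plan's own figures.** Sample size gives "1250 patients or 100 patients per month", then "we anticipate at least 80 % of consulters to be eligible (80 patients per month per practice"), then the share who will "provide consent and complete a baseline questionnaire (40 patients per month per practice").

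- 100 × 0.80 × 0.50 = 40 per practice per month
- 40 × 4 practices × 6 months = 960 at baseline, as stated
- 960 × 0.80 = 768 followed up, as stated
- m = 768/4 = 192 per practice

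For cost data, 192 is an upper figure. The brief questionnaire sent to non-responders at 6 and 12 months holds only the SF-36v2 and the global change item, so those participants supply no self-reported resource use.

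**Interval that treats participants as independent.** The article gives no ICC for costs, so a range is assumed.

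- Design effect: DE = 1 + (m − 1) × ICC = 1 + 191 × ICC
- Standard error understated by a factor of √DE
- True coverage of a nominal 95% interval: 2Φ(1.96/√DE) − 1
- Width of a practice-mean t interval (2 df, t = 4.30) relative to the naive one: √DE × 4.30/1.96

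| Assumed ICC | DE | √DE | Coverage | Relative width of 2-df interval |
|---|---|---|---|---|
| 0.001 | 1.19 | 1.09 | 93% | 2.4 |
| 0.005 | 1.96 | 1.40 | 84% | 3.1 |
| 0.01 | 2.91 | 1.71 | 75% | 3.7 |
| 0.02 | 4.82 | 2.20 | 63% | 4.8 |
| 0.05 | 10.55 | 3.25 | 45% | 7.1 |

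*Sensitivity to m.* Take 168 per practice, which is 70% of 240 (the 6-month retention that the protocol would accept). At ICC 0.01, DE = 1 + 167 × 0.01 = 2.67 and coverage is about 77%. At ICC 0.05, DE = 9.35 and coverage is about 48%. The picture does not depend on the exact follow-up.

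**Check with skewed costs.** Simulation of 1,500 trials with gamma-distributed costs, 192 per practice, two practices per arm, no true effect and 400 resamples per bootstrap:

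| Method | ICC 0 | ICC 0.01 | ICC 0.05 |
|---|---|---|---|
| Bootstrap of participants | 94% | 75% | 45% |
| Bootstrap of whole practices | 67% | 67% | 67% |
| Practice means, t on 2 df | 95% | 95% | 95% |

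A smaller run (600 trials, 300 resamples) of a two-stage bootstrap, practices and then participants, gave 91% at ICC 0.01 and 78% at 0.05.

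**Why resampling practices fails.** Drawing two practices with replacement from two gives only three possible arm means: the lower, the average and the higher, with probabilities 1/4, 1/2 and 1/4. Each extreme difference has probability 1/4 × 1/4 = 6.25%, which exceeds 2.5%. The percentile interval therefore runs from one extreme to the other. It misses zero exactly when both practices in one arm lie above both in the other. With no effect and exchangeable practices, that is 2 of the 6 possible splits of four practices into two pairs, so coverage is 1 − 2/6 = 67% whatever the ICC.

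These calculations take practices of equal size and do not model the stratification by practice size.

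**The case against.** The strongest reply is that the article is silent rather than wrong. It names no resampling unit, and bootstrapping is only an example. The text is compatible with a cluster-adjusted analysis, and Trial organisation and monitoring refers to a statistical analysis plan that is not shown. The authors plainly know about clustering: they commit to CONSORT for cluster trials, fit a practice random effect, and warn that an ICC from four practices will be unreliable. A reader might infer that the plan prescribes resampling participants and ignores practice. The article does not say that.

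This part of the reply stands, but it does not dispose of the point. The article does commit to an interval and a type of method, chosen on skewness alone, and naming the resampling unit later would not rescue it. Of the three percentile bootstraps tried, whole-practice resampling covers about 67% and two-stage resampling still falls short.

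Other objections also hold:

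- The economic analysis is exploratory and mainly descriptive. Calling it a test of costs overstates it.
- The stated progression criteria concern recruitment, retention and the self-referral share. None rests on a cost difference.
- A reader might infer that the method will be carried into the main trial. Nothing says so.
- The ICC is assumed, and at 0.001 the loss of coverage is slight.
- A 2-df interval is so wide that it may tell the reader little. That is why giving no between-arm interval is an equally acceptable repair.

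**Conclusion.** The point holds in a limited form. The economic section plans 95% intervals and, for skewed costs, a comparison of means such as a bootstrap, with no stated allowance for practice in a trial of four randomised practices, while the clinical section makes that allowance.

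If participants were treated as independent, coverage would be close to nominal at an ICC of 0.001 (93%), clearly short at 0.005 (84%) and poor at 0.01 and 0.05 (75% and 45%). This rests on assumed ICCs and on about 192 participants per practice. The failure of a whole-practice bootstrap (about 67%) does not depend on the ICC.

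The documents do not support saying that the cost intervals will certainly be far too narrow, because neither the cost ICC nor the resampling unit is given. The consequence is confined to the precision reported for the early cost difference. Recruitment, retention and the other feasibility conclusions are untouched.

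**What to change.** In Health economic analysis, replace the sentence on non-normal data with wording such as:

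*Costs will be described by practice and by arm. Either no between-arm interval will be given, or any such interval will be based on practice-level mean costs, using a t distribution with 2 degrees of freedom. Bootstrapping will not be used for between-arm cost intervals in this pilot. The cost analysis of the main trial will account for clustering by practice.*

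This needs no new data. The price is that between-arm cost intervals are either absent or much wider: about 3.7 times the naive width at an ICC of 0.01 and 7.1 times at 0.05. That width reflects what two practices per arm can show.
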